## Background

Aneurysmal subarachnoid hemorrhage (aSAH) is a highly fatal disease with a high incidence rate, accounting for about 80% of cases of SAH [1], and 46% of aSAH survivors suffer from long-term cognitive impairment [2]. Approximately one third of patients require lifelong care, which greatly affects their quality of life and places a tremendous burden on society [3].

Due to the complex pathophysiology of aSAH, it is often associated with ischemic and hemorrhagic complications. Although early treatment of aneurysms has become the primary means of preventing rebleeding, postoperative neurological complications are also common, including vasospasm, hydrocephalus, and rebleeding [4]. Cerebral vasospasm (CV) is the most severe and dangerous complication in the early stages of hemorrhage, typically occurring within 3–14 days following the onset of bleeding. The incidence of vascular spasm accounts for 40–70% of cases of aSAH and remains a significant factor contributing to morbidity and mortality [5]. It restricts blood flow and increases the risk of ischemia. Treatment options for CV include calcium channel blockers and endovascular therapy, as well as maintaining circulatory blood volume [6]. In addition to these treatments, the potential of heparin to reduce the incidence and mortality of aSAH-induced CV has gradually been explored, and it has also been shown to have anti-inflammatory and neuroprotective properties [7].

Unfractionated heparin (UFH) is a safe and commonly used anticoagulant, typically employed for the prevention of venous thrombosis and hypercoagulable states. It primarily functions by increasing the activity of antithrombin III to inhibit the activity of thrombin and factor Xa, thus preventing the formation of blood clots [8]. However, one of the side effects of heparin is bleeding, which necessitates coagulation function monitoring during its use.

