### Interventions, administration and duration

As part of the trial design, all enrolled patients will receive intervention following embolization of the aneurysm. The UFH group will start intravenous infusion of UFH 24 h after the embolization procedure, upon confirmation of inactive bleeding through head CT scan. The heparin will be administered at a dose of 8–10 U/kg/h, and APTT values will be monitored twice a day for 7 consecutive days. The infusion rate of heparin will be adjusted based on APTT values to maintain it within the range of 35–45 s. In case of APTT values exceeding or falling below the set range, the infusion rate will be decreased or increased by 1 IU and maintained for 12 h. As per FDA standards for the use of low molecular weight heparin, the UFH group will receive subcutaneous injection of prophylactic dose of LMWH (4000 IU) every 12 h for a duration of 1 week starting 24 h after the aneurysm repair.

All experimental UFH is stored in original packaging at 15–30 °C (protected from light and heat). LMWH is stored at 2–8 °C. After opening for more than 24 h, heparin should be discarded. During the administration process, the nursing staff is trained on medication usage and provided with dosing instructions and adverse reaction management plans for both the UFH and LMWH group. To ensure blinding, any communication between the research staff and participants that may reveal group allocation should be avoided. The identity of the medication provider should also not be disclosed.

During hospitalization, both groups of patients will be closely monitored for vital signs and symptoms in the intensive care unit. Platelet-inhibiting agents, nonsteroidal anti-inflammatory drugs, and oral anticoagulants are prohibited during the patient’s treatment period. Physicians will check for interactions with heparin when using other medications and closely monitor bleeding symptoms, adjusting the dosage of heparin or other medications as needed. All patients will receive oral nimodipine, and the blood volume will be maintained in equilibrium. The intracranial pressure of all patients will be monitored with the transducer. Transcranial Doppler (TCD) ultrasound will be performed daily to evaluate for CV, and a weekly follow-up head CT will be performed. In cases where CV or increased intracranial pressure is suspected, urgent head CT angiogram (CTA) or CT scans will be performed for confirmation.

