### Outcome assessments

#### Baseline assessment

Baseline variables encompass demographic information (gender, age, ethnicity, prior medical history, personal life history), comorbidities, vital signs (blood pressure, heart rate, respiratory rate), concomitant medication, surgical intervention (e.g., decompressive craniectomy), and results of the laboratory tests. In addition, Hunt-Hess scales [14] and World Federation of Neurosurgery Societies (WFNS) [15] grade were used to assess the severity of clinical symptoms. Modified Fisher score [16] was employed to evaluate the degree of CV. Assessment of functional independence was performed by the Modified Rankin Scale (mRS) [17]. All clinical baseline data were conducted upon admission and during hospitalization by two researchers who were unaware of the group assignment.

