### Primary and secondary outcomes

The primary outcome was the incidence of CV, while secondary outcomes included the incidence of bleeding events, ischemic events, HIT, deep vein thrombosis, cerebral venous circulation time, brain edema score, and incidence of hydrocephalus. The time points for the primary outcomes are the first and second weeks following the patient’s hospitalization and intervention treatment. The time points.for the secondary outcomes include the first 3 days after hospitalization, the first and second weeks, and the follow-up within 1 year after discharge. The CV was defined as the presence of significant neurological deficits in patients, with TCD ultrasound assess a mean flow velocity of the middle cerebral artery (MCA) exceeding 120 cm/s or a Lindegaard ratio (mean flow velocity of MCA/mean flow velocity of extracranial internal carotid artery) greater than 6. Computed tomography angiography scans showed temporary narrowing of cerebral artery. Regardless of the severity or clinical status of the patient, it was evaluated as CV.

Bleeding events are defined as bleeding that occurs in any part of the body, including intracerebral hemorrhage, gastrointestinal bleeding, and subcutaneous bleeding. According to the standardized bleeding score of Bleeding Academic Research Consortium (BARC), it has 5 types [18]. Type 1 refers to bleeding that is considered insignificant and does not prompt the patient to seek medical attention. Type 2 bleeding includes any obvious sign of hemorrhage that requires medical attention, diagnostic testing, hospitalization, or treatment by a healthcare professional. Type 3 bleeding encompasses clinical, laboratory, and/or imaging evidence of bleeding that requires a specific response from a healthcare provider. Type 4 bleeding is related to coronary artery bypass grafting within 48 h, and type 5 bleeding is fatal. Fatal bleeding can be categorized as intracranial, gastrointestinal, retroperitoneal, pulmonary, pericardial, genitourinary, or other.

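### If the primary outcome keeps a neurological deficit element, that deficit need be neither new nor attributable to vasospasm, and the article leaves open whether a deficit or CTA narrowing is required at all

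*Protocol article*

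**What the plan says.** All elements of the definition stand in the protocol article, Primary and secondary outcomes:

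- **Clinical element:** "The CV was defined as the presence of significant neurological deficits in patients".
- **TCD element:** "with TCD ultrasound assess a mean flow velocity of the middle cerebral artery (MCA) exceeding 120 cm/s or a Lindegaard ratio" above 6.
- **CTA element**, as a separate sentence: "Computed tomography angiography scans showed temporary narrowing of cerebral artery". The text does not say whether this is an added requirement or an alternative.
- **Closing sentence:** "Regardless of the severity or clinical status of the patient, it was evaluated as CV".
- **Timing:** "The time points for the primary outcomes are the first and second weeks" after hospitalization and intervention.

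Other sections bear on how the clinical element would work:

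- Interventions, administration and duration provides daily TCD and, when CV or raised intracranial pressure is suspected, "urgent head CT angiogram (CTA) or CT scans will be performed for confirmation".
- Baseline assessment says that Hunt-Hess and WFNS "grade were used to assess the severity of clinical symptoms". These scales, and the mRS, are not linked to the outcome definition.
- Background says that "postoperative neurological complications are also common, including vasospasm, hydrocephalus, and rebleeding".
- Inclusion criteria and Exclusion criteria exclude no severity grade. Recruitment lets a representative consent for patients who cannot.

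**The concern.** The clinical element asks only that a significant deficit be present. It names no reference examination and no attribution rule. This population often arrives with deficits, and the article itself names complications other than vasospasm that produce them.

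Three things follow if the deficit element is kept:

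1. **The outcome means different things by admission grade.** A patient with a deficit at entry has already met the clinical element and is classified on TCD/CTA findings alone. A good-grade patient must have those findings and also deteriorate.
2. **The arm difference may be diluted.** This happens if heparin type affects new deficits more than it affects velocity or narrowing in patients who already have a deficit.
3. **Harm may be counted as lack of efficacy.** A deficit from a heparin-related hemorrhage satisfies the same wording. Bleeding and hydrocephalus are separate secondary outcomes, and no rule keeps them apart from CV. If hemorrhage differs by arm, this misclassification differs by arm too.

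**Working it through.** **Step 1. Readings of the definition, side by side.**

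| Reading | Who counts as CV | Do onset and cause of the deficit matter? |
|---|---|---|
| Deficit and TCD | Any deficit plus velocity > 120 cm/s or Lindegaard > 6 | Yes |
| Deficit and TCD and CTA | As above, plus narrowing | Yes: an entry deficit still meets the clinical element, and narrowing does not show what caused the deficit |
| (Deficit and TCD) or CTA | Either route | Yes, on the first route |
| Closing sentence governs | TCD and/or CTA findings, with or without a deficit | No: the deficit clause does nothing |

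The gap exists on the first three readings and vanishes on the fourth. The article does not say which applies.

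**Step 2. Illustration of dilution.** The article gives no share of patients with an entry deficit and no TCD-positive rate among them, so these are assumptions.

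- Evaluable per arm: 228 × 0.9 ≈ 205 (228 per group and 10% dropout, from Sample size estimation).
- Assumed CV rate among patients without an entry deficit: 35% LMWH v 25% UFH.
- Assumed share with an entry deficit: d = 0.2 to 0.5.
- Assumed TCD-positive rate in that share: 50% on LMWH and 50% − e on UFH, where e is the UFH effect on that rate.

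Observed rates:

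- LMWH: p₁ = (1 − d) × 0.35 + d × 0.50
- UFH: p₂ = (1 − d) × 0.25 + d × (0.50 − e)

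Power, two-sided 5%, normal approximation, with p̄ = (p₁ + p₂)/2:

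Φ{ [ (p₁ − p₂)√n − 1.96√(2p̄(1 − p̄)) ] / √(p₁(1 − p₁) + p₂(1 − p₂)) }

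With d = 0 (35% v 25%, n = 205) power is 0.60. For d = 0.2 and e = 0: p₁ = 0.28 + 0.10 = 0.38 and p₂ = 0.20 + 0.10 = 0.30, a difference of 8 points.

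| d | e = 0: difference, power | e = 5 points: difference, power | e = 10 points: difference, power |
|---|---|---|---|
| 0.2 | 8.0 points, 0.40 | 9.0 points, 0.49 | 10 points, 0.58 |
| 0.3 | 7.0 points, 0.31 | 8.5 points, 0.44 | 10 points, 0.57 |
| 0.4 | 6.0 points, 0.24 | 8.0 points, 0.39 | 10 points, 0.56 |
| 0.5 | 5.0 points, 0.18 | 7.5 points, 0.34 | 10 points, 0.55 |

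If CTA is also required, the positive rate among entry-deficit patients would be lower. At an assumed 20–30% with e = 0, power is 0.44–0.42 at d = 0.2 and 0.21–0.20 at d = 0.5.

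**Step 3. Illustration of the bleeding route.** Assume an excess of 2 to 5 points in hemorrhage with deficit in one arm, half of those patients TCD-positive. That gives 2 × 0.5 = 1 to 5 × 0.5 = 2.5 points gross. Some would have had CV anyway. At CV rates of 35% to 25%, and assuming independence, the net addition is 1 × (1 − 0.35) = 0.65 to 2.5 × (1 − 0.25) ≈ 1.9 points. The article gives no hemorrhage rate by arm.

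**The case against.** **A reader might infer that any deficit counts as CV once TCD exceeds 120 cm/s.** The text does not support that as a fact. The CTA sentence may be a required element, and the plan to confirm suspected CV by urgent imaging favours that reading. The Lindegaard ratio is a second TCD route. If the closing sentence governs, no deficit is needed and its cause is irrelevant. This objection stands, so the point is conditional on a deficit element being kept. It does not remove the point: requiring CTA leaves the entry-deficit asymmetry in place, and the confirming scan may be plain CT.

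**A reader might also infer a large, certain loss of power, or cases fixed before treatment.** Neither is supported. Only the deficit can be present at entry; the TCD criterion must still be met during follow-up. The large losses need UFH to have little or no effect on velocity in these patients, although velocity is the protocol's own vasospasm measure. With an equal 10-point effect almost nothing is lost. Some entry-deficit cases will also have true vasospasm.

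**The article condenses a fuller protocol, which may hold adjudication detail.** That is possible, and Baseline assessment already has two assessors unaware of allocation recording clinical data on admission and during the stay. But the article does state the primary-outcome rule, and applied as written that rule admits old and unrelated deficits. It is a faulty stated rule rather than an omitted detail.

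**Conclusion.** The concern holds in conditional form. The definition contradicts itself on whether a deficit is needed and leaves the role of CTA narrowing open. If a deficit is needed, the rule has no onset or attribution requirement, so its strictness depends on admission grade, and deficits from hydrocephalus, rebleeding or heparin-related hemorrhage can enter the primary outcome. That follows from the text alone.

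The size does not. Under the assumptions in the working, power goes from 60% to anywhere between 58% and 18%, depending mainly on whether UFH lowers velocity in patients with an entry deficit. The bleeding route adds roughly 0.65 to 1.9 points under its own assumptions. These figures show sensitivity and are not estimates for this trial. The case for change rests on the meaning of the sole primary outcome more than on the power figures.

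**What to change.** In Primary and secondary outcomes:

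1. State whether a neurological deficit is required, and reconcile the opening clause with the closing sentence.
2. State whether CTA narrowing is an AND or an OR.
3. If a deficit is required, define it as new or worsened compared with the last examination before study heparin, and not explained by hemorrhage, rebleeding, hydrocephalus or another cause on imaging or chart review. A patient with a fixed entry deficit then counts only on worsening.
4. If a deficit is not required, delete the deficit clause.

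The cost is a sentence or two in the definition and a case report form field, using examinations and scans already planned. No treatment changes. The small downside is that the CV rate may fall below the 58–60% quoted in Sample size estimation, so the planning rates need rechecking against the final definition. The change belongs before recruitment, because redefining the outcome after enrolment would invite the charge of a post hoc choice.

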In patients undergoing endovascular treatment for aSAH, continuous maintenance of arterial catheters with UFH during surgery contributes to the reduction of thrombus formation, while subcutaneous injections of low-molecular-weight heparin (LMWH) prevent formation of lower-extremity deep veinous thrombosis. However, both LMWH and UFH infusions have their pros and cons. Although neurocritical care guidelines recommend initiating subcutaneous heparin 24 h after aneurysm embolization surgery [9], the UFH injection has limitations due to its high molecular weight and low bioavailability. Intravenous UFH may, therefore, be considered more reliable.

Research indicates that low-dose intravenous UFH infusion yields favorable outcomes in reducing CV and ischemic complications. Multiple retrospective studies have demonstrated the safety and efficacy of low-dose continuous intravenous UFH infusion. However, there is controversy regarding the optimal dosage and duration of treatment. A retrospective study by J. Marc Simard revealed the safety of low-dose (8–9 U/kg/h) intravenous UFH administration in aSAH patients, without any cases of bleeding, heparin-induced thrombocytopenia (HIT), or deep vein thrombosis, and the incidence of clinical vasospasm significantly decreased compared to subcutaneous LMWH usage [10]. Another research by Markus Bruder in endovascular treatment for aSAH patients showed a lower probability of cerebral infarction when combining UFH with LMWH [11].

Regarding the timing of initiating of heparin, Annika’s study suggested that using heparin within 24 h after aneurysm repair might be safer and carry a lower risk of bleeding compared to initiating treatment 48 h later [12]. Randomized controlled trial results comparing subcutaneous injections of LMWH and intravenous infusion of UFH are currently lacking, although randomized controlled studies have shown the safe and effective reduction of CV and ischemia with subcutaneous injection of enoxaparin compared to placebo in patients with aSAH [13].

This study is a single-center exploratory randomized controlled trial comparing the impact of low-dose intravenous infusion of UFH and subcutaneous injection of LMWH on the incidence of CV in aSAH patients. The outcomes to be assessed also include the occurrence of bleeding events, ischemic events, HIT, deep vein thrombosis, cerebral venous circulation time, brain edema score, and hydrocephalus incidence.

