Ischemic events include cerebral and cardiac ischemia, with cerebral ischemia encompassing transient ischemic attacks and stroke, while cardiac ischemia includes angina pectoris and myocardial infarction. HIT is defined as a decrease in platelet count of 50% or more after the therapy of heparin. Deep venous thrombosis includes lower limb deep venous thrombosis and pulmonary embolism, which is diagnosed by a respiratory physician based on pulmonary vascular examination and blood D-dimer testing. The diagnose of lower limb deep venous thrombosis is detected by ultrasound. Hydrocephalus is defined as an enlargement of the cerebral ventricles as visualized on a brain CT scan.

Cerebral venous circulation time is defined as the time required for blood to enter the venous sinus through the deep and superficial veins of the brain and then be drained into the jugular vein, including microvascular cerebral circulation time, venous cerebral circulation time, and the PRECISE score. Following S. Wang’s research, the starting point T1 is set as the first image in the sagittal view of digital subtraction angiography (DSA), which depicts the contrast dye within the branches of the middle cerebral cortical arteries [19]. The vein image that shows the peak filling of the parietal cortical vein is set as T2, and the only disappearance of the sigmoid sinus was set as T3. The mCCT is expressed as T2-T1, while vCCT is expressed as T3-T2.

The PRECISE score is based on the venous filling level shown on the head CTA. A score of 2 represents complete filling that is consistent with the degree of filling in the contralateral hemisphere, while a score of 1 represents partial filling, and a score of 0 indicates no filling. The filling difference of the affected hemisphere veins is calculated based on the PRECISE score. A higher score indicates the improved cerebral venous outflow, while a lower score signifies the decreased cerebral venous outflow. A score of 2 will be given for “complete” contrast filling of the opposite hemisphere, while a score of 1 will be given for “partial” (moderate contrast filling). The PRECISE score will be calculated using the composite score of the normal hemisphere SMCV + VOT + VOL + BVR minus the composite score of the lesioned hemisphere SMCV + VOT + VOL + BVR [20].

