### Safety assessments

To ensure the safety of the trial, it is imperative to closely monitor the patient’s condition, including changes in consciousness and vital signs. Laboratory and imaging tests are also necessary to promptly detect any adverse reactions associated with the drug, such as HIT and cerebral hemorrhage leading to cerebral herniation. Any confirmed adverse outcomes will be reported to the DSMC. In the event of a high risk of severe cerebral hemorrhage and cerebral herniation, emergency craniotomy or hematoma evacuation surgery is necessary. A decrease in platelet count is a direct manifestation of HIT. If a sharp decrease in platelet count is observed, heparin use should be immediately stopped. Common rescue drugs for severe HIT include immunoglobulin and plasma exchange.

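### HIT is defined by a platelet fall of 50% or more alone, so falls from other causes would be counted as HIT and blur the UFH versus LMWH safety comparison

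*Protocol article*

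**What the plan says.** The protocol article lists HIT among the trial's outcomes: "secondary outcomes included the incidence of bleeding events, ischemic events, HIT, deep vein thrombosis" and others. The definition, in the same section, is one sentence: "HIT is defined as a decrease in platelet count of 50% or more after the therapy of heparin".

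No time points are specific to HIT. The section says that the time points for the "secondary outcomes include the first 3 days after hospitalization, the first and second weeks, and the follow-up within 1 year after discharge". These are shared by all secondary outcomes and are not counted from a heparin dose.

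On exposure, Interventions, administration and duration says: "The UFH group will start intravenous infusion of UFH 24 h after the embolization procedure". The stated course lasts about a week.

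On the reference count, Baseline assessment includes laboratory results and says: "All clinical baseline data were conducted upon admission and during hospitalization". It does not say which platelet count the 50% is measured from.

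**The concern.** The sentence is worded as a definition and gives a numeric threshold. The same paragraph goes into diagnostic method for pulmonary embolism and leg vein thrombosis, so the article does work at this level of detail. The question is therefore what the stated rule does when it is followed, rather than what has been left to a fuller document.

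The rule makes any halving of the platelet count after heparin a case of heparin-induced disease. These patients have had a brain haemorrhage and an endovascular procedure and are in intensive care. Bleeding, fluid dilution, infection and consumption can all lower platelets, and nothing in the rule separates such falls from an effect of heparin.

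What is at stake is a safety comparison between two heparins. If the count mixes HIT with other thrombocytopenia, the reported HIT incidence is too high in each arm, and a real difference between UFH and LMWH is harder to see.

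**Working it through.** **1. Does any visible text narrow the definition?**

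| Element | What the article gives |
|---|---|
| Threshold | Fall of 50% or more |
| Reference count | Implied to precede heparin; sample not named |
| Onset window | None tied to heparin; generic time points to one year after discharge |
| Other causes | Not excluded |
| Antibody result, clinical score or case review | None described |
| Entry criteria | Severe thrombocytopenia excluded at entry; silent on later falls |
| Safety assessments | Calls a platelet decrease a direct manifestation of HIT; does not narrow the outcome |

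Nothing narrows it.

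**2. What does the timing allow?** Study heparin begins a day after embolization and runs for about a week. The earliest secondary time point, "the first 3 days after hospitalization, the first and second weeks" being the in-hospital sequence, starts at hospitalization, so it may contain little or no study heparin. The latest lies up to a year after discharge. A fall long after a one-week course still comes after heparin in the literal sense of the rule.

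**3. What does misclassification do to the comparison?** The article gives no HIT rate to reproduce, so this is an illustration and every rate in it is assumed. Let h be the true HIT risk in an arm and b the risk of a fall of 50% or more from another cause, taken as equal in both arms and independent of HIT.

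Counted rate = 1 − (1 − h)(1 − b)

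Take h = 2% for UFH and 0.5% for LMWH, with 228 per arm (Sample size estimation). For b = 5%:

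- UFH: 1 − 0.98 × 0.95 = 0.0690, or 228 × 0.0690 = 15.7 cases
- LMWH: 1 − 0.995 × 0.95 = 0.05475, or 228 × 0.05475 = 12.5 cases
- Relative risk: 0.0690 / 0.05475 = 1.26
- Share not HIT: (0.0690 − 0.02) / 0.0690 = 71% for UFH; (0.05475 − 0.005) / 0.05475 = 91% for LMWH

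| b (assumed) | Counted cases, UFH v LMWH | Relative risk | Risk difference, 1.5 × (1 − b), points | Power, two-sided 0.05 |
|---|---|---|---|---|
| 0% | 4.6 v 1.1 | 4.0 | 1.500 | 30% |
| 1% | 6.8 v 3.4 | 1.99 | 1.485 | 19% |
| 3% | 11.3 v 7.9 | 1.42 | 1.455 | 12% |
| 5% | 15.7 v 12.5 | 1.26 | 1.425 | 9% |

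With assumed true rates of 3% and 1%, the relative risk falls from 3.0 at b = 0% to 1.32 at b = 5%.

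Randomization and blinding gives 143 per arm instead of 228. The relative risks do not depend on arm size. At 143 per arm, power in the first scenario goes from 21% at b = 0% to 7% at b = 5%.

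The absolute difference hardly moves. What suffers is the incidence in each arm, the relative risk and the precision.

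**The case against.** **The article is condensed.** Onset windows, antibody testing and case review often sit in a full protocol, and the assessment schedule in Table 1 is not shown here. This stands for the sampling schedule. It does not cover the definition, which is stated as complete and would be applied as stated.

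**A reference count is implied.** A decrease after heparin presupposes a count before it, and laboratory results are collected at baseline. This stands: only the choice of sample is open.

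**Randomization protects the comparison.** Causes present at baseline should be balanced, so the expected effect is inflation and dilution, with no built-in advantage to one arm. This stands as the main expectation. A reader might infer that background falls would dominate or reverse the HIT difference. That needs a further difference between arms in bleeding or dilution. The Abstract does say that continuous intravenous heparin is debated because of bleeding, but no document gives such a difference for this trial.

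**Even a perfect definition has little power.** At the assumed rates power is 30% at best. This is true, but the counted incidence would still carry the wrong label.

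Two further inferences are tempting, and the documents support neither:

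- *Patients already exposed before the study drug.* Background says that "continuous maintenance of arterial catheters with UFH during surgery contributes to the reduction of thrombus formation". That describes endovascular treatment in general. The intervention section does not say that trial patients receive procedural UFH, so the exposure cannot be taken as fact.
- *Two conflicting HIT thresholds.* Safety assessments reads: "A decrease in platelet count is a direct manifestation of HIT. If a sharp decrease in platelet count is observed, heparin use should be immediately" (the sentence ends by calling for discontinuation). That is a safety trigger, whereas the definition sets a threshold for counting an outcome, and the two can coexist.

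**Conclusion.** The concern holds in limited form. The outcome labelled HIT is a platelet-fall outcome: it excludes no other cause and has no onset window linked to heparin. Followed as written, it would count falls of 50% or more from bleeding, dilution, infection or consumption as HIT. This raises the reported HIT rate in both arms and blurs the UFH versus LMWH comparison.

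The size is unknown, because the documents give neither the true HIT rate nor the rate of other falls of this size. The illustration shows direction and sensitivity only, and assumes an equal, independent background in the two arms. Background reports one retrospective study of low-dose UFH with no HIT cases. If true HIT were that uncommon here, most counted cases would be something else, but one retrospective report does not establish that for this trial.

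The primary outcome is unaffected. The point is worth correcting because it concerns a named safety outcome and costs little to change.

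**What to change.** 1. Report the existing criterion under its own name: *platelet fall of 50% or more from the last count before any heparin*. This fixes the reference sample and needs no assumption about procedural heparin.
2. Reserve *HIT* for the subset of these patients in whom existing outcome assessors, blinded to arm, judge HIT likely by a prespecified clinical pretest score. They would use routinely collected data: size of the fall, its timing relative to heparin exposure, thrombosis, any other evident cause, and any antibody result from routine care.
3. Present both by arm, so that the platelet-fall comparison is kept in full.

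No new assessor, test or visit is required, and no rule for stopping or changing treatment is proposed.

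The cost is a change of outcome wording and a short form for the few patients with such a fall. Fewer events will be labelled HIT, so that comparison will rest on smaller counts. The scoring also depends on dated platelet counts being available, which the visible text does not confirm.
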